### Sample Size

We will recruit 1,000 individuals using Prolific, which is the maximum sample size permitted for a nationally representative sample via this platform. This sample size will give allow us to detect small (Cohen’s d=0.18) differences between both groups with 80% power. This effect size would be more than sufficient for both analysis types, that is, LMM (linear mixed models) and path analyses, thus accounting for power and other sample size considerations common to path analysis (eg, overspecification) [61].

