### Conceptual Framework for the Proposed Study

Our prior research on COVID-19 misinformation identified 4 different COVID-19 belief profiles [17]. The “scientific” profile was the most common (~70% of the respondents), comprising individuals who reported high believability for a statement about the zoonotic origin of COVID-19 and low believability for misinformed narratives. The other 3 “nonscientific” profiles were not named and were instead numbered alongside conceptual descriptions. Profile 2 (~8% of the respondents) comprised individuals who reported high believability for all narratives, including the zoonotic statement and misinformed statements. Profile 3 (~12% of the respondents) comprised individuals who reported moderate believability for all narratives, and the lowest believability for the zoonotic statement of any profile (although it was still reasonably high, with a mean score of 4.59 on a scale of 1-7). Finally, Profile 4 (~10% of the respondents) was similar to Profile 2, except for a comparatively lower endorsement of the narrative that 5G networks caused the spread of COVID-19. Trust in science (a scale variable, scored from 1 to 5, and computed from a 21-item questionnaire) [37] was substantively associated with different profile memberships, after controlling for political orientation, religious commitment, race and ethnicity, gender, age, and education level. Compared to the scientific profile, each 1-point decrease in trust in science was associated with 5 (for Profile 3) to 14.3 (for Profiles 2 and 4) times higher adjusted odds of belonging to nonscientific profiles [17]. Therefore, we speculate that intervening at the level of trust in science will potentially nudge some individuals into the scientific profile.

However, whether trust in science will further affect individuals’ intention to engage in preventive NPBs via mediated beliefs in misinformation remains to be clarified. To the extent that some common narratives suggest that COVID-19 does not pose a serious health threat [17], such narratives may reduce the magnitude of “perceived severity” based on the health belief model. It is also notable that cross-sectional studies have suggested an association between perceived severity, self-efficacy, and COVID-19 NPBs in Turkey and Kenya [31,32].

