### Study Aims and Hypotheses

This study will accomplish the following 3 aims:

#### Aim 1

We aim to assess the effect of a brief informational infographic about the scientific process on trust in science. *We hypothesize that exposure to such an intervention will have a moderate, positive effect on trust in science*.

#### Aim 2

We aim to assess the effect of a brief informational infographic about the scientific process on the likelihood of believing scientifically implausible narratives about COVID-19. *We hypothesize that exposure to such an intervention will have a small, negative effect on the likelihood of believing implausible narratives, as evidenced by profile membership, and that this will be partly mediated by trust in science*.

#### Aim 3

We aim to assess the effect of a brief informational infographic about the scientific process on behavioral intentions to engage in recommended COVID-19 NPBs. *We hypothesize that exposure to such an intervention will have a small, positive effect on behavioral intentions to engage in recommended COVID-19 NPBs that will be partly mediated by misinformation profile membership*.

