### Allocation of Interventions

The allocation sequence will be managed using the Randomizer tool in the Qualtrics platform [62] to ensure a 1:1 allocation of participants to intervention (1) and control (0) arms, each comprising 500 participants. Allocation will occur after consent has been processed. Furthermore, the procedure is automated, thereby ensuring allocation concealment.

Although this is, in practice, a double-blind study since participants will be unaware that they are randomized and all study mechanics will be processed using a computer, analysts will not be blinded to the meaning of the assignment variable. However, 2 independent consultant analysts have been retained to verify all results and subsequent interpretation.

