#### Analyses

The following analyses will be performed for the 3 aim statements:

**Aim 1**: We will use an LMM to examine the effect of the intervention on trust in science, controlling for specified covariates (see Covariates).

**Aim 2**: We will first examine the profiles of believability in our control and intervention group using latent profile analyses [65,66]. After determining the number of classes and identifying scientific versus nonscientific profiles, we will conduct path analyses linking the brief digital intervention to believability profiles and the mediator (trust in science).

**Aim 3**: We will first examine the outcome variables for Aim 3—intention to engage in NPBs. Although we expect these intention-based items to function as a monotonic scale that can be collapsed into a single variable, we will need to conduct exploratory factor analysis to determine whether this is the case. The number of factors identified will affect how this outcome is treated in the subsequent part of Aim 3.

We will also examine the mediation effect of believability profiles on the association between behavioral intentions, trust in science, and the primary outcome for Aim 3 (ie, intention to engage in NPBs) in the post-test. Next, we will conduct path analyses linking the brief digital intervention to believability profiles and the mediators (trust in science and believability profiles), and behavioral intentions in the post-test.

For both Aims 2 and 3, we will use model fit statistics (eg, root mean square error of approximation, comparative fit index, and Tucker-Lewis Index) and examine specific indices of ill fit (eg, modification indices). To increase power and maintain Type I error, we will adapt the posterior probability method (eg, partial *P* value) for formal mediation analyses with intervening variables [67]. We aim to elucidate key mediational chains between our mediators (ie, trust in science and believability classes), predictors (ie, behavioral intervention statement), and outcome (ie, intention to engage in NPBs) through this design, instead of simply looking at the link between the intervention and intention to engage in NPBs.

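### The d=0.18 power statement is extended to the path analyses without support: for the Aim 2 profile outcome a shift of that size has about 56–63% power, not 80%

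*Protocol article*

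**What the plan says.** In the protocol article, Sample Size, the number recruited is set by the platform: "We will recruit 1,000 individuals using Prolific, which is the maximum sample size permitted for a nationally representative sample via this platform". Allocation of Interventions divides them into two arms, "each comprising 500 participants". The only power figure is "d=0.18) differences between both groups with 80% power". The next sentence extends it: "This effect size would be more than sufficient for both analysis types, that is, LMM (linear mixed models) and path analyses". No separate calculation is given for the path models.

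Those models carry Aims 2 and 3. Under Analyses, Aim 2 fits latent profiles and, after "identifying scientific versus nonscientific profiles", links the intervention to profile membership with trust in science as mediator. Aim 3 adds behavioural intention as the outcome, with trust and profile membership as mediators. Study Aims and Hypotheses expects small effects for Aims 2 and 3. For Aim 1 it expects that the intervention "will have a moderate, positive effect on trust in science". The Conceptual Framework section supplies a planning value for the profile split: the scientific "profile was the most common (~70% of the respondents").

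**The concern.** Cohen's d is a standardised mean difference. The Aim 2 outcome is a category, and with a 70/30 split a category carries less information than a continuous score, so the same underlying shift is harder to detect. The article has the 70% figure but does not use it in its power statement.

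What is at stake is how a null result is read. A reader who takes the sentence at face value would treat a non-significant Aim 2 result as evidence against an effect as small as d=0.18. The same applies to the Aim 3 path that starts with the intervention's effect on profile. The design does not have the stated power for either.

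**Working it through.** **Inputs.** 500 per arm (Allocation of Interventions); d=0.18 and 80% power (Sample Size); control share of the scientific profile 70% (Conceptual Framework, from the earlier study). Alpha is not stated; two-sided 5% is assumed because it reproduces the figure (one-sided 5% would give d=0.157).

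**1. The plan's own figure.** Detectable d = (1.960 + 0.842) × √(2/500) = 2.802 × 0.0632 = 0.177. Power at d=0.18 is Φ(0.18/0.0632 − 1.960) = Φ(0.886) = 81%. The sample for exactly 80% is 2 × (2.802/0.18)² ≈ 485 per arm. The figure reproduces as a two-sample comparison of a continuous score, with little to spare.

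**2. The same shift on the profile outcome.** Two standard conversions from 70%:
- Logistic: OR = exp(0.18 × π/√3) = 1.386. Odds 0.70/0.30 = 2.333 become 3.234, so the share is 3.234/4.234 = 76.4%.
- Probit: Φ(0.524 + 0.18) = Φ(0.704) = 75.9%.

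**3. Power for that shift.** Power = Φ[(Δ − 1.960 × SE₀)/SE₁], with SE₀ = √(2p̄(1−p̄)/500) and SE₁ = √((p₀q₀ + p₁q₁)/500).
- 70% v 76.4%: (0.0638 − 1.960 × 0.02802)/0.02794 = 0.319, power 62.5%.
- 70% v 75.9%: (0.0594 − 1.960 × 0.02809)/0.02803 = 0.155, power 56.2%.

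For 80% power these shifts would need 755 and 877 per arm. A conventional small d=0.20 has 65–71% power at 500 per arm.

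**4. What is detectable at 80%.** With 500 per arm the formula gives 70% v 77.8%: a 7.8-point difference, OR 1.50, Cohen's h 0.177. In d terms this is ln(1.50) × √3/π = 0.22 (logistic) or 0.24 (probit).

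**5. Sensitivity to the split.** The profiles are not prespecified, so the share may differ. Power at d=0.18-equivalent, probit to logistic:

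| Control share | Power |
|---|---|
| 50% | 62–73% |
| 60% | 60–70% |
| 70% | 56–63% |
| 80% | 49–50% |

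**6. The profile-first path in Aim 3.** A joint-significance test of intervention → profile → intention needs both links significant, so its power cannot exceed that of the first. Simulation with 500 per arm, an assumed intention gap between profiles of 0.5–1.0 SD and no classification error gives about 55–63% at the d=0.18-equivalent shifts and about 80% at 70% v 77.8%. The second link is nearly always significant, so the first link sets the power.

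**7. Paths through trust.** The Conceptual Framework gives odds ratios of 5 to 14.3 per point of trust. The SD of trust is not given; 0.4–0.8 points is assumed. The implied profile odds ratio is 5^(d×SD) to 14.3^(d×SD).
- Trust moves by d=0.18: OR 1.12–1.47, power 13–76% for the profile difference.
- Trust moves by d=0.5 (one reading of moderate): OR 1.38–2.90, power 61% to about 100%.

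In simulation the full trust–profile–intention chain had about 81% power at a trust effect of d=0.18, and near 100% at d=0.5, with strong later links and no classification error.

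**The case against.** The best defence is that the shortfall depends on the effect metric. Measured as Cohen's h, the proportion counterpart of d, the detectable shift is also about 0.18, so a small standardised effect in that sense does have 80% power. This is correct and should be acknowledged. But the article states d, and d=0.18 on an underlying scale is a smaller shift in proportions (h about 0.13–0.14).

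The defence also notes that mediation tests can be more powerful than a raw comparison of arms, that trust is measured before as well as after exposure, and that the trust effect is hypothesised to be moderate. All of this stands, and it limits the point: not every path test is underpowered.

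Two stronger readings are tempting. A reader might multiply a 7.8-point profile shift by an intention gap of 0.5–1.0 SD, obtain d of about 0.04–0.08, and conclude that the mediated part of Aim 3 has only 9–23% power. That is the power of a raw two-arm difference in intention. The article plans formal mediation tests, which with the same inputs reach about 80%. A reader might also infer that 80% at d=0.18 is a ceiling for every mediated path. That fixes the trust effect at d=0.18, which the hypotheses do not do.

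Finally, the sample size is at the platform maximum, so no recruitment decision turns on this. That is true, and it makes the point one about the stated power rather than the size of the trial.

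**Conclusion.** The concern holds for Aim 2 and for the path that runs first through profile membership. The calculation itself is right; extending it to path analyses is unsupported. At a 70% scientific share, power for a d=0.18-equivalent shift is about 56–63%, and 80% power requires about 70% to 77.8% (OR 1.50, d-equivalent 0.22–0.24). The profile-first path in Aim 3 can do no better than its first link.

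A direct total effect of d=0.18 on a single continuous intention score is covered, so the article does not misstate power for all of Aim 3. Power for paths through trust depends on inputs the article does not give and may be adequate.

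The Aim 2 figures rest on two-sided 5%, the earlier study's 70% share, reading d on an underlying continuous scale, and error-free classification. Misclassification would lower power. Covariate adjustment could raise it, though profile membership and intention have no baseline measure.

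**What to change.** In Sample Size:
- Limit the d=0.18 statement to two-group comparisons of a continuous score, namely Aim 1 and the Aim 3 total effect, and state the alpha.
- For Aim 2, give the detectable shift as 70% to 77.8% (OR 1.50), conditional on a 70% control share and on the profiles actually found.
- Remove the claim that the effect size is more than sufficient for path analyses, or support it with simulated power for the planned mediation tests under stated inputs (trust effect and SD, trust–profile association, profile gap in intention, classification error).
- Commit to reporting indirect effects with confidence intervals.

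Optionally, add a supporting Aim 2 analysis of the mean of the misinformation items, which are already collected. If one normal score were simply cut at 70/30, the split would keep about φ(0.524)²/(0.7 × 0.3) = 58% of the information. Latent profiles are built from several items, so that figure is only a guide.

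The cost is a less favourable stated figure, plus one regression if the supporting analysis is added.

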### Recruitment

Participants will be recruited via the Prolific platform to ensure a nationally representative sample of the US is composed with regard to age, sex, and race and ethnicity. To ensure compliance with institutional review board requirements, the questionnaires and procedures (including the study information sheet) will be hosted securely within Indiana University’s Qualtrics platform. Prolific will refer the sampled individuals to the Qualtrics system. Thereafter, we will randomly generate a unique identification for each Qualtrics user and ask the participants to enter it into Prolific to verify that they have completed the survey. We anticipate the survey will take no more than 15 minutes to complete; compensation will be set by Prolific to be equitable but noncoercive for research. The proposed methodology mirrors the protocol we successfully used with mTurk in our previous works [17,21].

### Allocation of Interventions

The allocation sequence will be managed using the Randomizer tool in the Qualtrics platform [62] to ensure a 1:1 allocation of participants to intervention (1) and control (0) arms, each comprising 500 participants. Allocation will occur after consent has been processed. Furthermore, the procedure is automated, thereby ensuring allocation concealment.

Although this is, in practice, a double-blind study since participants will be unaware that they are randomized and all study mechanics will be processed using a computer, analysts will not be blinded to the meaning of the assignment variable. However, 2 independent consultant analysts have been retained to verify all results and subsequent interpretation.

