#### Believability Profiles

Next, participants’ “believability profiles” will be computed via a latent profile analysis of the believability measures described below, which will be administered after the infographic is viewed. The measures and approach used to conceptualize believability of misinformation were developed and first used in our recent study on COVID-19 narratives [17]. As in the original study, we will not prespecify the existence of certain profiles, although we do expect to identify similar profiles in this study (potentially with differences introduced by the additional metrics described subsequently).

Response options for all believability measures will use well-established semantic differential responses for believability of different statements (eg, as used by Herzberg et al [53]), ranging from 1 (“extremely unbelievable”) to 7 (“extremely believable”). The original measures [17] assessed the believability of 4 statements related to COVID-19 that were derived from common pieces of misinformation (as of April 2020), as identified by a team at Cornell University [54]. For instance, one of the statements was, “The recent rollout of 5G cellphone networks caused the spread of COVID-19.” Another statement asked subjects about their believability of a particular statement reflecting scientific consensus (ie, the zoonotic origin of the virus). Our ability to use latent profile analysis to generate plausible and conceptually meaningful subgroups with a good model fit points toward a certain degree of validity of these questions. This is noteworthy especially given the existence of a latent profile that generally believed the scientific consensus explanation and no other narrative (which would be less likely with invalid questions). Therefore, in this study, we will assess participants’ believability of the following 6 statements, which include slightly modified versions of the 4 above-referenced statements, as well as 2 new statements based on scientific findings clarifying emergent, persistent misinformation about the use of face masks to prevent COVID-19 spread [55-57]:

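### Analysts who know the arms will decide, from post-infographic data, what the Aim 2 and Aim 3 primary outcomes are

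*Protocol article*

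**What the plan says.** The Primary Study Outcomes section lists three outcomes: trust in science, believability profiles and behavioral intentions. The believability and intention items are given after the infographic is viewed.

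- **Profiles.** The Believability Profiles section says "we will not prespecify the existence of certain profiles", and adds that similar profiles to those of the earlier study are expected. The Analyses section, under Aim 2, says "We will first examine the profiles of believability in our control and intervention group using latent profile analyses". The number of classes and the scientific or nonscientific label are settled next, and the path analyses follow.
- **Intentions.** Under Aim 3 a single scale is expected, but an exploratory factor analysis decides: "The number of factors identified will affect how this outcome is treated in the subsequent part of Aim 3".
- **Blinding.** Allocation of Interventions says that "analysts will not be blinded to the meaning of the assignment variable", and that two independent consultant analysts will verify the results and their interpretation.
- **Indicators.** The Believability Profiles section announces the "believability of the following 6 statements". The list that follows it has seven.

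**The concern.** Measuring outcomes after exposure is normal. The weakness is that the *definition* of two primary outcomes is chosen after exposure, by people who can see the arms. Choosing between three and four classes, deciding whether a mixed profile counts as scientific, and choosing one intention score or two are all judgement calls on which fit statistics often do not give a clear answer. An analyst who can see how each option divides the arms may lean, without intending to, toward the one that shows a difference. The nominal error rate then no longer applies to the reported test, and a reader of the results cannot tell whether this happened.

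Two smaller defects affect the same outcome. The wording about profiles in the control and intervention group leaves open whether one model or two will be fitted. The stated number of indicators also does not match the list.

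**Working it through.** **1. The plan's own figure.** Sample Size says "We will recruit 1,000 individuals using Prolific" and claims power for "small (Cohen’s d=0.18) differences between both groups with 80% power". With 500 per arm and an assumed two-sided 5% level, power = Φ(d√(n/2) − 1.96) = Φ(0.18 × 15.81 − 1.96) = Φ(0.886) = 81.2%. The required size is 2(1.960 + 0.842)²/0.18² ≈ 485 per arm. The figure reproduces. It applies to one comparison of a continuous outcome fixed in advance, so it says nothing about how the Aim 2 and Aim 3 outcomes are built.

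**2. Who decides what, and when.**

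| Decision | Made from | Outcome affected |
|---|---|---|
| Number of profiles | Post-infographic believability items | Aim 2 outcome, Aim 3 mediator |
| Scientific or nonscientific label | The fitted profiles | Aim 2 outcome, Aim 3 mediator |
| Number of intention factors | Post-infographic intention items | Aim 3 outcome |

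The article describes no step that keeps the arm code from those making these decisions, and says outright that the analysts are not blinded.

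**3. Size in the worst case.** Assumptions not in the article: there are three candidate solutions, their z statistics share a common correlation ρ, there is no true effect, and the solution that reaches significance is the one reported. Then

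P(any |z| > 1.96) = 1 − ∫ φ(u) [Φ((1.96 − √ρ·u)/√(1−ρ)) − Φ((−1.96 − √ρ·u)/√(1−ρ))]³ du.

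| ρ | Error rate |
|---|---|
| 0.5 | 12.5% |
| 0.7 | 10.9% |
| 0.9 | 8.4% |
| 0.95 | 7.3% |

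**4. Cross-check with the article's profile shares.** The Conceptual Framework section gives about 70%, 8%, 12% and 10%. A null simulation (100,000 runs, 500 per arm) compared the arms on the scientific profile alone, and on that profile merged with one other. One fixed definition gave 5.0%. A free choice among two, three or four definitions gave 8.3%, 11.2% and 13.8%.

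**5. Aim 3.** The six intention items were split, by assumption, into a pair (distance, mask) and the other four. Reporting whichever of the full scale or the two sub-scales is significant gave 9.4% at an inter-item correlation of 0.3 and 8.4% at 0.5.

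**6. If profiles were fitted separately by arm.** Suppose the class boundaries drifted so that the share labelled scientific differed with no true effect, starting from 70%. A two-proportion test with 500 per arm would reject in about 10% of trials for a 2-point drift, 29% for 4 points and 57% for 6 points. The drifts are assumed; they show only why the wording needs settling.

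**7. Item count.** The text describes four modified earlier statements plus two new ones on masks, 4 + 2 = 6. The list holds four misinformation statements carried over (5G, vaccination programs, military weapon, exaggerated deaths), two on masks, and the animal-origin statement: 4 + 2 + 1 = 7. The seventh is the item on which the earlier scientific profile scored high.

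**The case against.** The strongest reply is that the choices are less open than they look. The Conceptual Framework section describes the four earlier profiles, including the scientific one and its approximate share. The Believability Profiles section expects similar ones, and the Analyses section names a single intention scale as the expected form. The unblinding is disclosed, and two outside analysts check the work. All of this is fair, and it makes a fully free choice unlikely. But an expectation is not a rule: the article expressly declines to prespecify profiles and lets the factor count change the Aim 3 outcome. Nothing says that the consultants are blinded, and their stated task is to verify results.

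A second reply is that such detail belongs in a statistical analysis plan, which is not shown. That would answer a complaint about something omitted. This point rests on what the article states: unblinded analysts and data-driven definitions.

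Two stronger readings are tempting and should not be adopted.

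- **That profile membership will be treated as known without error.** A reader might infer this from the order of steps, classes first and path models after. The article never says so. The same order fits an analysis that carries classification uncertainty forward, and the method for doing so is commonly left to an analysis plan. No loss of power can be charged to the plan on this ground.
- **That separate models by arm are planned.** This is possible but the weaker reading. The article speaks of one latent profile analysis and one number of classes, and then links the intervention to membership, which requires a variable common to both arms. It is a wording to clarify, not a stated error.

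**Conclusion.** The point holds as a modest, cheaply repaired weakness: unblinded analysts settle the class number, the labels and the intention scoring on post-infographic data, and those choices fix two of the three primary outcomes. For Aim 3 the freedom in the outcome itself is the factor count; the profiles enter there as a mediator.

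The worst-case error is about 7% to 13% in place of 5%, for three candidate solutions with correlation from 0.95 down to 0.5. A reader might take this as the trial's actual error rate. It is not: it requires that the most favourable solution be picked, and the number of candidates and the correlation are assumed. No figure in the article is shown to be wrong by it.

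The six-against-seven mismatch is certain but minor, since every item is printed in full.

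**What to change.** 1. Export the analysis file without the arm column.
2. State that one latent profile model is fitted to all randomised participants pooled, and reword the Aim 2 sentence to match.
3. Lock in a dated memo the number of classes, the scientific or nonscientific label of each, and the intention score or factor count.
4. Only then merge the arm code and run the path models.
5. Correct the number of believability statements from six to seven, and state that the animal-origin item is one of the profile indicators.

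The profiling and the factor analysis stay exploratory, as intended. The cost is holding back one column until the memo is signed, plus two small text corrections. No added participants or data collection are needed.
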